### Data management

All clinical data for this study will be managed using the data management system of the Shunyi Branch of Beijing Hospital of Traditional Chinese Medicine, and regular data audits will be conducted. Serious adverse events and unexpected events will be reported promptly to the Ethics Committee and regulatory authorities in accordance with regulations. Progress reports will be submitted on schedule, detailing adverse events, subject withdrawals, and protocol deviations. The principal investigator will conduct periodic cumulative reviews of all adverse events and, if necessary, convene investigator meetings to assess the risks and benefits of the study.

### Data analysis

#### Imaging data analysis

The rs-fMRI data will be preprocessed using SPM12 (https://www.fil.ion.ucl.ac.uk/spm/) and DPARSF 5.0 toolkit (56) with Matlab 2020a. Data preprocessing includes the first ten time points removed to allow for magnetization equilibrium, slice timing correction, realignment for head motion correction (subjects with head motion exceeding 2 mm in translation or 2° in rotation will be excluded), spatial normalization to Montreal Neurological Institute (MNI) space and resampled at 3 mm × 3 mm × 3 mm voxel size, spatial smoothing with a 6 mm full-width at half maximum Gaussian kernel, linear detrending, nuisance covariates regression (including 24 head motion parameters, white matter signals, and CSF signals), and band-pass filtering (0.01–0.08 Hz).

After standard preprocessing, ReHo, ALFF, and fALFF analyses will be calculated to explore regional brain activity. For FC analysis, seed regions will be defined based on brain areas showing significant differences in ALFF, fALFF, or ReHo analyses, and the mean time series of each seed region will be correlated with the time series of all other voxels across the whole brain using Pearson’s correlation coefficients, which will be subsequently transformed to z-values using Fisher’s r-to-z transformation to improve normality (57). Two-sample Student’s t-tests and paired Student’s t-tests will be conducted respectively to examine the differences in taVNS-related central responses between groups and within groups. The results will be corrected by Gaussian Random Field (GRF) Theory (voxel-level *P* < 0.005, cluster-level *P* < 0.05) (58).

Structural 3D-T1WI data processing will be performed using two complementary approaches. For VBM, the CAT12 toolbox (http://www.neuro.uni-jena.de/cat/) implemented in SPM12 will be employed. Data preprocessing includes bias-field correction, tissue segmentation into GM, White Matter (WM), and CSF maps, spatial normalization to Montreal Neurological Institute (MNI) space using the Diffeomorphic Anatomical Registration Through Exponentiated Lie Algebra (DARTEL) algorithm, modulation to preserve the total amount of tissue within each voxel, resampling at 1.5 mm × 1.5 mm × 1.5 mm voxel size, and spatial smoothing with an 8 mm Full-Width at Half Maximum (FWHM) Gaussian kernel. For SBM, cortical reconstruction and parcellation will be performed using FreeSurfer (ver. 7.2; https://surfer.nmr.mgh.harvard.edu/). The processing pipeline includes motion correction, intensity normalization, skull stripping, automated tissue segmentation, identification of the white matter and pial surfaces, cortical surface inflation and registration to a spherical atlas, and cortical parcellation based on the Desikan-Killiany atlas (59). CT will be computed as the shortest distance between the white matter and pial surfaces at each vertex, and cortical surface area (CSA) will be calculated as the total area of the cortical mantle at each vertex. Surface maps will be smoothed with a 10 mm FWHM Gaussian kernel. Two-sample Student’s t-tests and paired Student’s t-tests will be applied to examine inter-group and intra-group differences in GMV, CT, and CSA, respectively. VBM results will be corrected by GRF Theory (voxel-level *P* < 0.005, cluster-level *P* < 0.05), and SBM results will be corrected using the Monte Carlo cluster-wise correction method (cluster-forming threshold *P* < 0.001, cluster-level *P* < 0.05) (60).

ASL data processing will be performed using SPM12 and the ASLtbx toolbox (https://www.nitrc.org/projects/asltbx/). Preprocessing includes motion correction of the ASL time series, co-registration to the individual 3D-T1WI structural image, pairwise subtraction between labeled and control images to generate perfusion-weighted images, and quantitative CBF map calculation using the single-compartment model in accordance with the consensus recommendations (61). The CBF maps will then be spatially normalized to MNI space using the transformation parameters derived from the structural image normalization, resampled at 2 mm × 2 mm × 2 mm voxel size, and spatially smoothed with a 6 mm FWHM Gaussian kernel. Two-sample Student’s t-tests and paired Student’s t-tests will be conducted to examine the between-group and within-group differences in regional CBF, respectively. The results will be corrected by GRF Theory (voxel-level *P* < 0.005, cluster-level *P* < 0.05). Across all imaging modalities, these thresholds were applied to control the family-wise error rate; GRF correction was used for the voxel-wise analyses (rs-fMRI, VBM, and ASL), whereas the Monte Carlo cluster-wise method was adopted for the surface-based analyses (CT and CSA) because it is better suited to the geometry of the cortical surface. These criteria follow widely adopted neuroimaging conventions, balancing protection against false positives with sensitivity to true taVNS-related effects.

Additionally, Pearson’s correlation analyses will be performed to explore the relationships between changes in neuroimaging indicators (ALFF, fALFF, ReHo, FC, GMV, CT, CSA, and CBF) and changes in clinical outcome measures (PSQI, NIHSS, ADL, HAMD-17, and HAMA-14), with statistical significance set at *P* < 0.05 (Bonferroni-corrected). For these brain-behavior correlations, the mean values of each neuroimaging metric will first be extracted from the clusters showing significant between- or within-group differences in the preceding voxel- or vertex-wise analyses; these extracted values, rather than whole-brain maps, will then be correlated with the corresponding changes in clinical scale scores. Pearson’s correlation will be applied when both variables satisfy the assumptions of normality and linearity, and Spearman’s rank correlation will be used otherwise. The taVNS and sham-taVNS groups will be analyzed separately, and the Bonferroni method will be used to correct for the number of correlation tests performed.

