**Methods/design:**

This single-blind randomized controlled trial will enroll 48 patients with PSI, randomly assigned in a 1:1 ratio to a taVNS group or a sham-taVNS group. Both groups will receive the assigned intervention once daily, five days per week, for four weeks, in addition to standard post-stroke basic treatment. The primary outcomes are multimodal magnetic resonance imaging (MRI) indicators acquired before and after the 4-week intervention, including resting-state functional MRI (amplitude of low-frequency fluctuation, fractional amplitude of low-frequency fluctuation, regional homogeneity, and functional connectivity), three-dimensional T1-weighted structural metrics (gray matter volume, cortical thickness, and cortical surface area), and arterial-spin-labeling cerebral blood flow. The secondary outcomes are clinical efficacy scales, namely the Pittsburgh Sleep Quality Index, the National Institutes of Health Stroke Scale, the Activities of Daily Living scale, the 17-item Hamilton Depression Rating Scale, and the 14-item Hamilton Anxiety Rating Scale, assessed at baseline, week 2, and week 4. Between- and within-group differences will be examined using two-sample and paired t-tests with Gaussian random field correction for imaging data and repeated-measures analysis of variance for clinical data, and Pearson or Spearman correlation analyses will relate neuroimaging changes to clinical improvement.

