### Outcome measures

#### Primary outcomes

The primary outcomes include neuroimaging indicators derived from fMRI, 3D-T1WI, and ASL, specifically: The primary outcome is defined as the change in these multimodal MRI indicators from baseline to the end of the 4-week intervention; the principal comparison is the between-group difference in these changes (taVNS vs. sham-taVNS), with within-group pre-to-post changes assessed as a secondary contrast. The specific indicators are as follows:

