###### Regional homogeneity

ReHo is based on Kendall’s coefficient of concordance and evaluates the similarity between a target voxel and its neighboring voxels over a time series on a voxel-by-voxel basis (39). This method is widely used in the analysis of changes in local spontaneous neural activity in neuropsychiatric disorders, as well as in studies of the central mechanisms of taVNS (40).

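### ReHo is calculated on time series already smoothed at 6 mm, which imposes part of the concordance it measures and can cost sensitivity

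*Protocol article*

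**What the plan says.** ReHo is one of the primary indicators. The Primary outcomes section states: "The primary outcomes include neuroimaging indicators derived from fMRI, 3D-T1WI, and ASL". The abstract names the rs-fMRI set as "amplitude of low-frequency fluctuation, fractional amplitude of low-frequency fluctuation, regional homogeneity, and functional connectivity".

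The Regional homogeneity section bases ReHo on Kendall's coefficient of concordance and says that it "evaluates the similarity between a target voxel and its neighboring voxels over a time series on a voxel-by-voxel basis".

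The Imaging data analysis section gives a single rs-fMRI preprocessing list. Data are normalised and "resampled at 3 mm × 3 mm × 3 mm voxel size". The list continues with "spatial smoothing with a 6 mm full-width at half maximum Gaussian kernel", then detrending, nuisance regression and a 0.01–0.08 Hz band-pass. The next paragraph opens: "After standard preprocessing, ReHo, ALFF, and fALFF analyses will be calculated to explore regional brain activity". ReHo therefore shares one stream with ALFF and fALFF. No unsmoothed branch for ReHo is described, and no later smoothing of the ReHo maps.

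The same section lets significant ReHo clusters serve as FC seeds, and takes values from significant clusters into the correlations with the clinical scales.

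**The concern.** ReHo asks how far a voxel's time series agrees with those around it. A Gaussian kernel with a width of two voxels mixes exactly those series before the question is asked. Some agreement is then present whatever the brain is doing, and true differences in local coherence sit on top of an imposed offset.

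What is at stake is sensitivity. The trial has 24 patients per arm, and its own Discussion concedes that power may be limited. The Discussion also predicts increased ReHo in the prefrontal cortex and precuneus. If the pipeline has weakened the metric, a null ReHo result would be hard to interpret, and fewer or different ReHo clusters would feed the FC and correlation analyses.

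**Working it through.** **Inputs from the protocol.** Kernel 6 mm FWHM; voxels 3 mm; 200 time points in Table 1, less "the first ten time points removed to allow for magnetization equilibrium", leaves 190; TR 2000 ms; band-pass 0.01–0.08 Hz. **Assumptions.** A 27-voxel neighbourhood (the size is not stated; 7 is also shown), the spatial form of the signal, and the spread between patients. The protocol gives no ReHo figure to reproduce.

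**Step 1: concordance created by the kernel alone.** After smoothing independent noise, two voxels at distance d correlate as exp(−d²/(4s²)), with s = 6/2.3548 = 2.548 mm.
- Face neighbours (d = 3 mm): exp(−9/25.97) = 0.71.
- Mean over all pairs in a 27-voxel block: 0.3226.
- Kendall's W ≈ (1 + (m − 1)·mean r)/m = (1 + 26 × 0.3226)/27 = 0.348. Without smoothing it is 1/27 = 0.037.
- With 7 voxels: about 0.59, against 1/7 = 0.14.

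Simulation with 190 volumes and the planned band-pass gives 0.037 unsmoothed and 0.33 smoothed at 6 mm. Allowing for trilinear resampling of 3.5 mm native voxels to 3 mm, the values are 0.14 and 0.42.

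**Step 2: mean ReHo when there is true signal.**

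| Signal share | Local field (8 mm), unsmoothed | Local, smoothed | Shared by all voxels, unsmoothed | Shared, smoothed |
|---|---|---|---|---|
| 0.1 | 0.084 | 0.509 | 0.137 | 0.839 |
| 0.3 | 0.175 | 0.579 | 0.335 | 0.948 |
| 0.5 | 0.265 | 0.601 | 0.526 | 0.976 |
| 0.7 | 0.365 | 0.607 | 0.714 | 0.989 |

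From share 0.3 to 0.7 the local-field spread falls from 0.365 − 0.175 = 0.190 to 0.607 − 0.579 = 0.028, a reduction of 85%. The shared-signal spread falls from 0.379 to 0.041, a reduction of 89%. These are changes of scale. A t-test is unaffected if the spread between patients shrinks in proportion, so standardised differences are needed.

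**Step 3: standardised differences, unsmoothed against smoothed first.**
- Shared signal, between-patient SD of share 0.08, rise of 0.1 from 0.1, 0.3 and 0.5: 1.07 to 0.91, 0.91 to 0.81, 1.04 to 0.86. Losses are 15%, 11% and 17%.
- Local signal, same settings: 1.02 to 0.86, 0.75 to 0.18, 1.12 to 0.47. Losses are 16%, 76% and 58%.
- Local signal, SD 0.05, with the usual order (ReHo, then map smoothing) as the comparator: 2.89 to 0.47 (share 0.3 against 0.5), 2.44 to 0.31 (0.5 against 0.7), 5.49 to 0.88 (0.3 against 0.7). Losses are 84%, 87% and 84%. The between-patient SD did not shrink here: 0.028–0.037 with the usual order, 0.046–0.060 with smoothing first.
- A further run with a rise of 0.1 gave about 1.0–1.2 falling to 0.1–0.4 for local signal, and a loss of 0–25% for shared signal.

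**The case against.** Four points can fairly be made against this.

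1. **No bias.** The kernel and the acquisition are the same for every scan, so the offset is common to arms and visits. It does not by itself create a false taVNS effect or raise the type I error. This stands.

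2. **Lost range is not lost power.** A reader might infer from the 85–89% compression, or from smoothed values of 0.91–0.99, that most of the power has gone. The shared-signal model refutes this: the range falls by 89% while the standardised difference falls by only 11–17%. Values near 1 also belong to that model, in which one signal spans the whole grid; with a local field smoothed ReHo stays near 0.6. This stands, which is why the size is given in standardised differences.

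3. **ReHo still responds to the brain.** A reader might infer that smoothed ReHo mainly measures the kernel. That depends on the signal model. At low signal shares smoothed ReHo still moves clearly (0.33 to 0.51 as the local share goes from 0 to 0.1), and the loss in the local model starting from a share of 0.1 was only 16%. The stronger statement is not supported.

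4. **Condensation.** A journal article may compress several metric-specific streams into one list. That is possible, and it limits certainty about how the data will be handled. But the article is not silent: it places smoothing before filtering and ReHo after the whole list, with no exception. If practice differs, the text is wrong.

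ReHo is also only one of eight imaging indicators, and FC seeds can come from ALFF or fALFF clusters. That limits the reach of the problem without removing it.

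**Conclusion.** The point holds as a flaw in the stated processing order, and it should be fixed. Smoothing before ReHo imposes part of the concordance that "evaluates the similarity between a target voxel and its neighboring voxels over a time series" is meant to capture: about 0.33 instead of 0.04 for independent noise, assuming 27 neighbours. The comparison between arms remains unbiased.

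The cost is possible loss of sensitivity, and its size cannot be fixed from the document. It is 0–25% of the standardised difference if signal is shared by all voxels, and roughly 60–90% if signal is spatially local and of moderate or greater strength, with smaller losses when local signal is weak. These figures rest on assumed signal models, neighbourhood size and between-patient spread, not on trial data. The effect reaches a primary indicator and whatever FC seeds and brain-behaviour correlations are drawn from ReHo clusters.

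**What to change.** In the Imaging data analysis section, state that ReHo is calculated on normalised, detrended, nuisance-regressed and band-pass-filtered but unsmoothed data, and that the ReHo maps are then smoothed with the same 6 mm kernel before the group tests. Smoothing before ALFF and fALFF can stay as planned. State the neighbourhood size as well.

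If this is already the intended practice, correct the stated order. Either way the change is a reordered step and a sentence or two of text. It needs no new data or extra scanning and should be settled before the primary imaging analysis.

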### Multimodal MRI data acquisition

All multimodal MRI data will be acquired on a Siemens 3.0T Vida scanner at the Shunyi Hospital of Beijing Hospital of Traditional Chinese Medicine. For each participant, scanning will be performed at two time points: on the day before the first treatment session and on the day after completing the 4-week intervention. To minimize variability, all scans will be obtained using identical hardware, sequences, and acquisition parameters at both time points.

Three sequences will be acquired in a fixed order. First, resting-state functional MRI (rs-fMRI) will be obtained using a gradient-echo echo-planar imaging (GRE-EPI) sequence to capture spontaneous neural activity. During the scan, participants will be instructed to remain awake with their eyes closed, stay as still as possible, and refrain from engaging in any structured thought. Next, a three-dimensional T1-weighted image (3D-T1WI) will be acquired to provide high-resolution structural information for morphometric analysis and for spatial normalization of the functional and perfusion data. Finally, arterial spin labeling (ASL) perfusion imaging will be performed to quantify cerebral blood flow. The detailed acquisition parameters for all three sequences are summarized in **Table 1**.

**Table 1 T1:** Acquisition parameters of the multimodal MRI sequences.

Parameter	rs-fMRI (GRE-EPI)	3D-T1WI	ASL
Repetition time, TR (ms)	2000	2530	4200
Echo time, TE (ms)	30	2.98	38.06
Flip angle, FA (°)	90	7	120
Field of view, FOV (mm)	224 × 224	256 × 256	224 × 224
Matrix	64 × 64	256 × 256	64 × 64
Slice thickness (mm)	3.5	1.0	3.5
Number of slices	32	192	46
Voxel size (mm³)	3.5 × 3.5 × 3.5	1.0 × 1.0 × 1.0	3.5 × 3.5 × 3.5
Number of time points	200	—	—
Acquisition time	6 min 46 s	6 min 3 s	7 min 21 s

rs-fMRI, resting-state functional MRI; GRE-EPI, gradient-echo echo-planar imaging; 3D-T1WI, three-dimensional T1-weighted imaging; ASL, arterial spin labeling; TR, repetition time; TE, echo time; FA, flip angle; FOV, field of view.

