##### fMRI

###### Amplitude of low-frequency fluctuation and fractional amplitude of low-frequency fluctuation

ALFF effectively reflects spontaneous neural activity in the cerebral cortex by calculating the average amplitude of low-frequency signal fluctuations, and is a commonly used method for analyzing signal characteristics of individual voxels or localized brain regions (36). This metric has been widely applied in studies of spontaneous brain activity under various conditions (37). fALFF is an improved analytical method based on ALFF. It effectively reduces the susceptibility of ALFF to physiological noise interference in the cerebral pool and ventricular regions, offering higher sensitivity and specificity for the detection of spontaneous brain activity (38).

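### As written, fALFF is calculated on data already band-pass filtered to 0.01–0.08 Hz, which makes it constant under an ideal filter and distorted under a gradual one

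*Protocol article*

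**What the plan says.** The abstract lists fALFF among the primary outcomes: "resting-state functional MRI (amplitude of low-frequency fluctuation, fractional amplitude of low-frequency fluctuation, regional homogeneity, and functional connectivity"). The Primary outcomes section adds that "The primary outcome is defined as the change in these multimodal MRI indicators from baseline to the end of the 4-week intervention", with the between-group difference in change as the principal comparison.

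Under Imaging data analysis, a single preprocessing list serves all rs-fMRI metrics. It drops the first ten volumes, then runs through slice timing, realignment, normalisation, smoothing, detrending and nuisance regression. It closes with "and band-pass filtering (0.01–0.08 Hz"). The following paragraph opens: "After standard preprocessing, ReHo, ALFF, and fALFF analyses will be calculated to explore regional brain activity".

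The section that introduces ALFF and fALFF presents fALFF as the better measure, less prone to physiological noise and "offering higher sensitivity and specificity for the detection of spontaneous brain activity".

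fALFF is used in three further places:
- regions that differ on ALFF, fALFF or ReHo become the FC seeds (Imaging data analysis);
- change in fALFF, extracted from significant clusters, enters the correlations with the clinical scales (Imaging data analysis);
- the Discussion predicts higher ALFF/fALFF in the prefrontal cortex and precuneus under taVNS.

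**The concern.** What separates fALFF from ALFF is its denominator. Dividing by amplitude over the whole measurable spectrum discounts voxels that are noisy at all frequencies. That only works if frequencies outside the low band are still in the data when the ratio is taken. The stated order removes them first.

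If the plan is followed literally, one primary indicator either cannot vary or measures something other than what is claimed for it. The fALFF part of the Discussion's prediction could not be properly tested. Because fALFF also contributes to seed selection, a distorted version could carry over into FC, which is another primary indicator.

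**Working it through.** **Inputs from the protocol article**
- Table 1: "Repetition time, TR (ms) 2000 2530 4200". The first value is the rs-fMRI sequence, so TR = 2 s.
- Table 1: "Number of time points 200" for rs-fMRI. Ten are discarded, leaving T = 200 − 10 = 190.
- Filter band: 0.01–0.08 Hz.
- The plan states no fALFF value, effect size or power, so there is no figure of its own to reproduce.

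**Assumed definition** (standard; the article gives no formula)

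fALFF = (sum of spectral amplitudes in 0.01–0.08 Hz) / (sum of amplitudes over all non-zero frequencies up to the highest detectable one).

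**Frequency bins**
- Highest detectable frequency: 1/(2 × 2 s) = 0.25 Hz.
- Bin spacing: 1/(190 × 2 s) = 1/380 = 0.00263 Hz.
- Non-zero bins: 0.25 × 380 = 95.
- Band limits in bins: 0.01 × 380 = 3.8 and 0.08 × 380 = 30.4, so bins 4 to 30, which is 27 bins.
- Out-of-band bins: 95 − 27 = 68.

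**Ideal filter.** The 68 out-of-band amplitudes become zero and the 27 in-band amplitudes are untouched. Numerator and denominator are then the same sum, and fALFF = 1 whatever the signal. This is algebra and needs no signal model.

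An illustration: give every bin amplitude 1 in voxel A, and double only the in-band amplitudes in voxel B.

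| | Voxel A | Voxel B |
|---|---|---|
| fALFF, unfiltered | 27/95 = 0.284 | 54/(54 + 68) = 0.443 |
| fALFF, after ideal filter | 27/27 = 1 | 54/54 = 1 |
| Mean in-band amplitude (ALFF), before or after | 1 | 2 |

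The voxels differ clearly on unfiltered fALFF and not at all on filtered fALFF. ALFF still separates them.

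**Gradual filter.** Here a signal model has to be assumed. 5,000 series (TR 2 s, 190 volumes) were simulated, each a different mixture of 1/f low-frequency signal and white noise, then detrended. The Butterworth filters were applied forwards and backwards.

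| Series used for fALFF | Mean | SD | Correlation with unfiltered fALFF |
|---|---|---|---|
| Unfiltered | 0.352 | 0.043 | – |
| Ideal 0.01–0.08 Hz | 1.000 | about 5e-17 (rounding) | not defined |
| Butterworth, design order 2 | 0.81 | 0.041 | 0.47 |
| Butterworth, design order 4 | 0.86 | 0.043 | 0.31 |

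Unfiltered fALFF correlated 0.71 with the simulated low-frequency signal weight, so it carries information. After a gradual filter the voxels still vary by about as much, but the variation largely reflects what leaks past the band edges. The sharper of the two filters gave the weaker relation. ALFF was identical before and after the ideal filter (maximum difference 0).

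**Downstream.** With an ideal filter every change score is 0 with no variance. No t-test can be formed and no cluster arises, so fALFF drops out of seed definition and of the correlations. With a gradual filter, clusters may arise, but on the distorted measure.

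**The case against.** The strongest reply is that the list is an inventory shared by four metrics in a condensed article. It does not name the filter type or say which series each metric uses. The team or its toolbox may well compute fALFF on unfiltered data, and step order per metric is often left to a fuller document. It is therefore fair to say that the text does not show that the analysis will be run wrongly. The reply does not remove the point, because the article does not leave the order open. It puts the filter inside preprocessing and the fALFF calculation after it. A correct analysis plan would contradict it.

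It can also be said that only one of eight primary indicators is directly affected, that FC can still be seeded from ALFF or ReHo, and that a map equal to 1 everywhere would be noticed. All of this is true and limits the damage. But the distorted values from a gradual filter would look plausible and would not reveal themselves in that way.

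A reader might go further than the documents allow in three ways:
- **That fALFF loses all information under any filter.** This holds for the ideal filter only; a gradual filter leaves a weak relation.
- **That spurious clusters will necessarily contaminate FC and the correlations.** A constant measure produces no clusters, so this cannot be combined with the ideal-filter result. Under a gradual filter it is possible but not certain.
- **That a specific loss of power follows.** The article gives no fALFF effect size or between-patient SD, so none can be derived.

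**Conclusion.** The point holds for the pipeline as stated. With an ideal filter fALFF is exactly 1 in every voxel, patient and visit, and neither the between-group nor the pre-to-post contrast can be tested. With a gradual filter it is pushed upwards (mean 0.81 to 0.86 against 0.352 unfiltered) and only weakly related to the intended measure (correlation about 0.3 to 0.5).

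The ideal-filter result rests only on the standard ratio definition. The gradual-filter figures also rest on the assumed signal model and indicate direction and rough size only.

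The defect is confined to fALFF and what is derived from it. It should not be read as undermining ALFF, whose in-band amplitudes an ideal filter leaves unchanged, or ReHo, which has no out-of-band denominator. The structural and perfusion outcomes are not involved.

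**What to change.** In Imaging data analysis, take the band-pass filter out of the common list and state:
- fALFF is computed on the detrended, nuisance-regressed but unfiltered series, with 0.01–0.08 Hz as the numerator band and the full range to 0.25 Hz as the denominator;
- the 0.01–0.08 Hz filter applies to the series used for ReHo and FC.

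ALFF may be taken from the same unfiltered series for consistency, but this is optional.

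The cost is a sentence or two and the order of toolbox steps, with no change to scanning and no new data. It should be settled before imaging data are processed, so that the definition of a primary indicator is not changed after results have been seen.

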Such integrated analyses are expected to identify specific neuroimaging biomarkers that can not only predict treatment responsiveness but also clarify the central mechanisms through which taVNS exerts its therapeutic effects. For example, the association between enhanced functional connectivity in the DMN and reduced PSQI scores may suggest that taVNS exerts its sleep-promoting effects by modulating large-scale neural networks involved in self-referential processing and arousal regulation (70). Similarly, the correlation between increased cerebral blood flow in the thalamus and prefrontal regions and improved sleep maintenance may indicate that the restoration of neurovascular coupling is one of its key mechanisms of action (71). Building on these prior mechanistic findings, we can make several specific predictions regarding the brain regions most likely to be modulated by taVNS in PSI. At the functional level, given that taVNS has been shown to normalize spontaneous activity and to enhance connectivity within the default mode network, thalamus, and prefrontal cortex in primary insomnia and depression (17, 40, 70), we anticipate that the taVNS group will show increased ALFF/fALFF and ReHo in the prefrontal cortex and precuneus, together with strengthened thalamo-cortical and intra-DMN functional connectivity. At the structural level, because chronic sleep deprivation is associated with gray matter atrophy in the hippocampus, prefrontal cortex, and anterior cingulate cortex (24, 25), a 4-week intervention may produce measurable increases, or attenuated loss, of gray matter volume and cortical thickness in these emotion- and cognition-related regions. At the perfusion level, taVNS is expected to increase cerebral blood flow in the thalamus and prefrontal cortex, reflecting restored neurovascular coupling in hypoperfused, sleep-regulating areas. We further hypothesize that these regional changes will correlate with clinical improvement, such that greater enhancement of prefrontal-thalamic function and perfusion is accompanied by larger reductions in PSQI and HAMD/HAMA scores. Specifying these candidate regions and directional hypotheses in advance strengthens the forward-looking value of the protocol and provides concrete, testable targets for the planned analyses.

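### Functional connectivity is a primary outcome, but its seeds exist only where other primary measures turn out significant in the same scans, so whether and where it is tested is not fixed in advance

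*Protocol article*

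**What the plan says.** The abstract of the protocol article defines the primary outcomes as multimodal MRI indicators, "including resting-state functional MRI (amplitude of low-frequency fluctuation, fractional amplitude of low-frequency fluctuation, regional homogeneity, and functional connectivity" among them. Under Primary outcomes, "the principal comparison is the between-group difference in these changes (taVNS vs. sham-taVNS), with within-group pre-to-post changes assessed as a secondary contrast".

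Under Imaging data analysis, ALFF, fALFF and ReHo are computed first. For FC, "seed regions will be defined based on brain areas showing significant differences in ALFF, fALFF, or ReHo analyses". Each seed's average signal is then related to every voxel outside it, which gives one brain map per seed. The tests follow: "Two-sample Student’s t-tests and paired Student’s t-tests will be conducted respectively to examine the differences in taVNS-related central responses between groups and within groups". Then: "The results will be corrected by Gaussian Random Field (GRF) Theory (voxel-level *P* < 0.005, cluster-level *P* < 0.05". At the end of its account of the ASL analysis, the same section says that the thresholds control the family-wise error rate across all imaging modalities.

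The Discussion predicts higher ALFF/fALFF and ReHo in the prefrontal cortex and precuneus, "together with strengthened thalamo-cortical and intra-DMN functional connectivity". It presents these regions and directions as set in advance and as targets for the planned analyses.

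**The concern.** A primary outcome should have a test that is defined before the data are seen. Here FC has no test until another primary measure produces a significant area. Three things follow.

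- **FC may have no test.** The section gives no atlas seed, independent sample or fallback for the case where the regional maps show nothing. The connectivity hypothesis written into the Discussion could then go unexamined.
- **The test is not independent of how its seed was chosen.** ALFF, fALFF, ReHo and FC all come from the same BOLD series in the same people. If a chance regional difference tends to come with a chance connectivity difference, an FC test run only at selected seeds rejects too often.
- **The number of seeds depends on the data.** Each selected area yields its own whole-brain map. The stated correction works within a map, not across maps.

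At stake is how an FC result, or the lack of one, can be read as primary evidence on mechanism.

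**Working it through.** **Inputs from the protocol article.** 24 participants per group (2 × 24 = 48, which agrees with the stated total); voxel-level P < 0.005 and cluster-level P < 0.05 per map; three screening measures (ALFF, fALFF, ReHo); one between-group and two within-group contrasts. The article gives no planning figure for the FC test, and no effect size, SD or power, so there is no stated FC figure to reproduce.

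**Assumptions.** Independence between maps and between seeds; the correlation rho between the regional statistic and the FC statistic; the standardised effect d. None is in the documents, so rho and d are shown as ranges.

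**1. Chance that no seed arises when nothing differs.** With m independent maps at 0.05, P(no seed) = 0.95^m.

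- Between-group maps only, m = 3: 0.95^3 = 0.857, so at least one seed in 0.143.
- Within-group maps counted too, m = 3 × 3 = 9: 0.95^9 = 0.630, so at least one seed in 0.370.

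The article does not say which of these applies. The maps share data; positive dependence would raise the no-seed chance.

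**2. The screen can also fail when a regional effect is real.** Two-sided power at a single voxel at P < 0.005, n = 24 per group, 46 degrees of freedom, noncentrality d × √(24/2) = 3.464d:

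| d (assumed) | noncentrality | power |
|---|---|---|
| 0.5 | 1.732 | 0.125 |
| 0.8 | 2.771 | 0.439 |
| 1.0 | 3.464 | 0.694 |

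These are single-voxel powers, not cluster powers, and serve only as an indication.

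**3. Error rate of the FC test given that its seed was selected, with no true effect.** Let the two statistics be bivariate normal, Z_FC = rho × Z_screen + √(1 − rho²) × E. Select when the screen has two-sided P < 0.005, then test FC at two-sided 0.05 (4 million draws):

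| rho (assumed) | P(FC significant, given selection) |
|---|---|
| 0 | 0.050 |
| 0.1 | 0.061 |
| 0.2 | 0.091 |
| 0.3 | 0.143 |
| 0.5 | 0.319 |
| 0.7 | 0.608 |

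**4. Multiplicity across seeds.** For k independent seeds each at cluster-level 0.05, family-wise error = 1 − 0.95^k: 0.143 for k = 3 and 0.226 for k = 5. This would arise even with seeds fixed in advance.

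**5. Seed rule against hypothesis.** The Discussion expects regional activity changes in the prefrontal cortex and precuneus, and connectivity changes along thalamo-cortical and default-mode paths. The thalamus is not among the regions where it predicts an ALFF, fALFF or ReHo change. So even if every regional prediction came true, the seed rule would not make the thalamus a seed.

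**The case against.** The strongest reply is that result-driven seeds are a reasonable way to explore, that an article may leave seed coordinates, a fallback and correction across seeds to an analysis plan not shown here, and that FC is one of eight primary indicators, the other seven being unaffected. The last part is true. The first two do not remove the point: the article itself fixes the rule, and applies it to an outcome it calls primary, so an analysis plan that followed it would inherit the problem.

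Several stronger readings are tempting and not supported.

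- *The FC maps are uncorrected.* They are not: Gaussian random field correction applies within each map. Only correction across seeds is unstated.
- *A thalamo-cortical or default-mode effect without an amplitude change can never be found.* Each seed is correlated with the whole brain, so the thalamus can appear as a target of a prefrontal or precuneus seed, and ReHo can select a seed without an amplitude change. Detection is not guaranteed; it is not impossible.
- *Seeds are chosen on the very contrast that FC then tests.* The text names no contrast, and selection is on a related statistic, not on FC itself.
- *FC false positives are inflated per trial by a known amount.* The inflation is conditional on a seed existing, is zero at rho = 0, and has no size that the documents can supply. As a rough guide for one seed from three between-group maps with no effect anywhere, 0.143 × 0.143 = 0.020 at rho = 0.3 and 0.143 × 0.319 = 0.046 at rho = 0.5, both below 0.05; at rho = 0.7 it is 0.143 × 0.608 = 0.087.

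**Conclusion.** The point holds as a should-fix. The article makes FC primary and then lets other primary results decide whether, where and how many times it is tested, without naming the contrast that defines a seed. The seed rule does not use the regions that the Discussion puts forward in advance. These conclusions rest on the text alone.

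The 86% and 63% no-seed figures hold only under a global null with independent maps; they do not forecast how often FC will go untested in a trial with real regional effects. That FC would then have no test is inferred from the absence of any other seed definition; the article does not say so. The conditional error of 9% to 32% for rho between 0.2 and 0.5 depends wholly on rho. The 14% and 23% for three and five seeds assume independent seeds, and they qualify the article's statement that its thresholds control the family-wise error rate.

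**What to change.** In Imaging data analysis, replace the seed rule for the primary FC analysis with seeds fixed in advance from a named atlas, drawn from the Discussion's own regions: thalamus, precuneus (default mode network) and one prefrontal node. State that the primary FC test is the between-group difference in change, with cluster-level P < 0.05 divided by the number of seeds. For three seeds that is 0.05/3 = 0.0167, giving a family-wise error of 1 − (1 − 0.0167)^3 = 0.049 if independent and at most 0.05 otherwise, provided each map holds its nominal level. FC is then tested whatever the regional maps show, and selection no longer affects its error rate. Keep seeds taken from significant ALFF, fALFF or ReHo areas as exploratory only, and name the contrast that defines them.

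The alternative is to keep the present rule and move FC as a whole to exploratory status.

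The cost is a sentence or two and no new data. The price is a stricter threshold per seed, and findings in unexpected regions become exploratory. The change has to be made before any unblinded imaging analysis, since seeds chosen after that cannot be called prespecified.
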